##### Secondary criterion D: changes in driving habits

2.3.2.2

Based on the results of the DHQ and DBQ questionnaires, changes in driving habits will be assessed using the difference scores between “before npABI” and M6 and M12 after the approved doctor’s opinion. These difference scores can be calculated on the basis of responses to each questionnaire item, as well as on the basis of each investigated dimension by grouping items (speed, duration, frequency, etc.).

##### Secondary criterion E: impact of pedagogical support

2.3.2.3

In the context of pedagogical support, the usefulness of the advice given will be analyzed using a 5-point Likert scale, ranging from “Very useful” to “Not at all useful.” The information can be collected globally, or by type of advice.

#### Statistical analysis

2.3.3

To meet the main and secondary A and B objectives, concordance tests will be used to verify that two independent abilities to resume driving measures (two tests) of the same modality—“Favorable” or “Unfavorable”—are equal. Concordance analyses between tests (binary variables) will be expressed in the form of concordance percentages, simple kappa coefficient and its 95% confidence interval. Analyses between TRIP (continuous variable) and other tests (binary variables) will be conducted using *t*-tests or Mann–Whitney tests depending on the TRIP score distribution. Multivariate regression will also be used to study measures’ concordance and prediction levels, for both objectives. It will be logistic or linear, depending on the studied variable (i.e., approved doctor’s opinion for objective A and TRIP results for objective B).

A sensitivity and specificity analysis of the approved doctor’s opinion will also be carried out. Performance metrics (Secondary Objective C) will be calculated from the confusion matrix values (Table 4):$$\mathrm{Accuracy:}\frac{RP+RN}{RP+RN+FP+FN}$$$$\mathrm{Sensitivity (Se):}\frac{RP}{RP+FN\text{.}}$$$$\mathrm{Specificity (Sp):}\frac{RN}{FP+RN}$$$$\mathrm{Positive predictive value (PPV) or Precision (Pr):}\frac{RP}{RP+FP}$$$$\mathrm{Negative predictive value (NPV):}\frac{RN}{FN+RN}$$

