Each rehabilitation center will recruit around 10 to 20 patients, up to a total of 100 participants. A post hoc sensitivity analysis was performed using G*Power Software Version 3.1.9.7 (Faul et al., 2007) to determine the minimum effect size that could be achieved with 100 participants. A post hoc power analysis for an independent-sample t-test was conducted assuming one-tailed testing. For effect size varying from large (d = 0.8) to small (d = 0.2), 80% power and alpha error probability of α = 0.05 a sample size interval of at least 12 to 156 participants is suggested. With a sample of 100 participants to be included in this study and 80% power the effect size is estimated at 0.25. Each participant must have a npABI and be between the ages of 21 and 65, in order to avoid confusing the issues of ageing and non-progressive acquired brain injury, people over 65 were excluded from the study and treated at their center for routine care. All participants must have held a Category B driving license (light vehicles) for at least 3 years and have driven a minimum of 10,000 km, so as not to assess novice drivers. They have been examined by the PRM doctor, who confirms that there are no contraindications to driving other than the pathology under study. They also gave their consent to take part in the PREVAC study. The ethical committee has classified this research as a non-interventional, involving no risk or constraint for participants, and in which all procedures are carried out in the usual way. They must not have a medical condition (other than npABI) that is incompatible with maintaining their driving license, according to the list of conditions mentioned in the decree of March 28, 2022. They must not have any oral comprehension disorders that can be perceived by the therapist, must not be pregnant (to avoid an interruption of pregnancy in the event of an accident and the resulting psycho-social and legal risks), and must not be under the influence of any Level 3 medication that could present a driving risk.

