##### Secondary evaluation criteria (criteria A and B)

2.3.1.2

A cross-sectional analysis of professional evaluations will be performed to meet the following secondary objectives:Study the concordance between each professional assessment (cf. main objective) and the approved doctor’s opinion concerning the participant’s ability to resume driving;Study the concordance between professional assessments (cf. main objective) and the TRIP

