###### Secondary criterion B: concordance professional assessment / TRIP grid

2.3.1.2.2

An analysis identical to the main objective will be carried out, cross-referencing the results of the professional assessments with that of the TRIP, expressed as a binary variable Favorable / Unfavorable (Table 3).

**Table 3 tab3:** Evaluation criteria of the secondary objective B for contingency table.

		Assessment x_i_	
		Favorable	Unfavorable
TRIP grid	Favorable	*a*	*b*
	Unfavorable	*c*	*d*

The TRIP score will also be analyzed continuously (total adjusted score out of 100), in total and by sub-score. Correlation analysis will also be carried out between the raw results from the neuropsychological tests and the TRIP grid, in order to identify the neuropsychological tools most predictive of driving ability in real-life situations.

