#### Relevance of on-road assessment

3.1.2

- In the event of concordance between opinion following RDA and other assessments (neuropsychological, multiprofessional, approved doctor’s opinion), the assessment tools mentioned can be considered to be good predictors of driving ability, in accordance with the literature (Marshall et al., 2007).- In the event of a discrepancy between RDA and other assessments, the RDA value will remain undeniable, but results can be explored and discussed depending on which assessment there is a discrepancy with, and the direction of this discrepancy. More specifically, a discrepancy between RDA and neuropsychological assessment can highlight coping strategies linked to awareness of cognitive disorders. In fact, correlation between neuropsychological assessment and actual driving may depend on the individual’s level of awareness of their abilities (Griffen et al., 2011). These results would not, therefore, call into question value of the RDA. On the other hand, a discrepancy between the opinion given following RDA and that given by the PRM doctor (multiprofessional evaluation) or the approved doctor may raise questions about value of the RDA, or at least the importance attached to it by doctors (PRM or approved doctor).- In the event of concordance between the TRIP score and the various assessments, TRIP can be considered a relevant tool for predicting driving ability. Conversely, in the event of discrepancies between TRIP and other assessments, the usefulness of this grid can be discussed. Further analysis could highlight the relevance of certain sub-scores.- In the event of concordance between the number of interventions on the controls and professional opinions, this criterion can then be considered to be a good predictor of driving ability. On the other hand, in the event of discrepancies, a certain tolerance may be accepted if the driving instructor intervenes on the controls during RDA.

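### The planned t-test or Mann–Whitney test on the continuous TRIP score shows association with the opinions, not discrimination, and no planned measure shows how well the 15 sub-scores sort drivers

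*Protocol article*

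**What the plan says.** Secondary objective B is to "Study the concordance between professional assessments (cf. main objective) and the TRIP". The plan approaches it in two ways.

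- **Binary TRIP.** Section 2.3.1.2.2 repeats the main analysis, "cross-referencing the results of the professional assessments with that of the TRIP, expressed as a binary variable Favorable / Unfavorable" (Table 3). Section 2.3.3 gives the measures: "Concordance analyses between tests (binary variables) will be expressed in the form of concordance percentages, simple kappa coefficient and its 95% confidence interval".
- **Continuous TRIP.** The same section adds: "The TRIP score will also be analyzed continuously (total adjusted score out of 100), in total and by sub-score". For this part section 2.3.3 says: "Analyses between TRIP (continuous variable) and other tests (binary variables) will be conducted using *t*-tests or Mann–Whitney tests". It also plans multivariate regression, logistic or linear, with the TRIP result as the outcome for objective B.

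Section 2.2.1.4 gives the grid 15 sub-scores and a total out of 100. On interpretation, section 3.1.2 says: "In the event of concordance between the TRIP score and the various assessments, TRIP can be considered a relevant tool for predicting driving ability". It then expects further analysis to bring out which sub-scores are relevant. It gives no threshold and does not say which of the two analyses decides.

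The abstract sets a wider aim: the cross-sectional study is to examine the sensitivity and specificity of the neuropsychological tests and of the on-road grid. Section 2.3.3 names sensitivity and specificity only for the approved doctor's opinion and for road risk (objective C).

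**The concern.** A two-group location test has as its null hypothesis that TRIP levels are equal in the favorable and unfavorable groups. Rejecting it shows that the groups differ on average. It says little about overlap, and overlap determines whether a score can sort one driver from another. Regression with TRIP as the outcome models the level of TRIP given the opinion, so it leaves the same gap.

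The sub-scores are the weak spot. They appear only in the continuous analysis, so for them a p-value or a difference in level would be the main evidence of relevance. The article leans towards reading significance as prediction elsewhere: section 3.1.1 treats neuropsychological tests that correlate significantly with TRIP as the most predictive, and section 3.2 uses similar language for road risk. The results are meant to underpin national recommendations and possibly the training of approved doctors, where sorting individuals is what matters.

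**Working it through.** The plan gives no AUC or misclassification figure to reproduce. The check asks how often a weakly discriminating score would be significant, and what the planned kappa would show for the same score.

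**Inputs from the article.** N: "up to a total of 100 participants" (section 2.1). Significance level 5% (section 2.3).

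**Assumptions not in the article.** Normal scores with equal variance in the two opinion groups, a two-sided test, a cut midway between the group means, all 100 participants analyzable, and opinion splits from 50/50 to 10/90.

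**Step 1: effect size for AUC 0.65.** d = √2 × z(0.65) = 1.414 × 0.385 = 0.545. At the midpoint cut, sensitivity = specificity = Φ(d/2) = Φ(0.272) = 0.607, so 39% are misclassified.

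**Step 2: power of the t-test.** Noncentrality = d × √(n₁n₀/N), with 98 degrees of freedom and critical value 1.984.

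**Step 3: kappa for the same score cut at the midpoint.** Observed agreement is 0.607 at every split. At 50/50, chance agreement is 0.500 and kappa = (0.607 − 0.500)/0.500 = 0.21. At 30/70, the TRIP-favorable share is 0.7 × 0.607 + 0.3 × 0.393 = 0.543, chance agreement is 0.543 × 0.7 + 0.457 × 0.3 = 0.517, and kappa = 0.090/0.483 = 0.19. The other splits follow in the same way.

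| Split | Noncentrality | P(significant) | Kappa |
|---|---|---|---|
| 50/50 | 0.545 × √25 = 2.725 | 0.77 | 0.21 |
| 30/70 | 0.545 × √21 = 2.497 | 0.70 | 0.19 |
| 20/80 | 0.545 × √16 = 2.180 | 0.58 | 0.15 |
| 10/90 | 0.545 × √9 = 1.635 | 0.37 | 0.09 |

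**Step 4: smallest significant difference at 50/50.** d = 1.984 × √(1/50 + 1/50) = 0.397. This is AUC Φ(0.397/√2) = 0.61, with Φ(−0.198) = 42% misclassified.

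**Step 5: fewer analyzable participants.** Missing data are not replaced. With 80 participants the probabilities for AUC 0.65 are 0.67 (50/50), 0.60 (30/70) and 0.49 (20/80). With 60 they are 0.55, 0.48 and 0.38.

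**Step 6: what an AUC interval would show.** Hanley–McNeil standard error for A = 0.65 and 50 per group, with a = A/(2 − A) = 0.4815 and b = 2A²/(1 + A) = 0.5121: SE = √{[0.2275 + 49(0.4815 − 0.4225) + 49(0.5121 − 0.4225)]/2500} = 0.055. The 95% interval is 0.65 ± 1.96 × 0.055, about 0.54 to 0.76. It excludes 0.5, in line with a significant test, but it also shows how weak the discrimination may be.

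**The case against.** The strongest reply is that the plan does not use the two-group test to measure agreement. Section 2.3.3 keeps the word concordance for percent agreement and kappa on binary variables, and the continuous TRIP analysis is an addition. For the total score this stands: a TRIP with AUC 0.65 would show kappa of about 0.2 or less, printed beside any significant t-test, so the weakness would be visible.

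A reader might infer that a TRIP misclassifying four in ten drivers will usually pass as a relevant tool. The article does not support that. No section equates a significant test with concordance, and the study is described as exploratory. The frequency also depends on assumptions outside the article: with 100 participants and AUC 0.65, the chance of significance falls to 0.37 at a 10/90 split.

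It is also fair that the AUC is the Mann–Whitney statistic divided by n₁n₀, so where that test is used the quantity is already within reach, and that an article need not list every summary. But the article does choose the test for the continuous score, and that choice answers a narrower question than sections 3.1.2 and the abstract pose.

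The reply does not cover the sub-scores. Table 3 concerns the TRIP as a whole, so kappa gives no safeguard for them. Nor does section 3.1.2 say which analysis governs if the two-group test and kappa point in different directions.

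**Conclusion.** The point holds as a limited one. The tests planned for the continuous TRIP show association only. A significant result should not be presented as concordance or as predictive relevance. For the total score, the planned kappa already limits the damage. For the 15 sub-scores no agreement or discrimination measure is named, although section 3.1.2 looks to their relevance.

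The size is illustrative: under equal-variance normal scores, N = 100 and a two-sided 5% level, AUC 0.65 is significant with probability 0.77 to 0.37 as the split moves from 50/50 to 10/90. Normality is least certain for the sub-scores. The logical point needs none of these figures. This is a cheap improvement in method, not a flaw that invalidates objective B.

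**What to change.** In section 2.3.3:

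- Report the AUC with its 95% confidence interval for the TRIP total and each sub-score, against each of the three professional opinions (neuropsychological, on-road, multiprofessional), beside the planned percent agreement and kappa.
- Report sensitivity and specificity from Table 3 for the total score, in line with the abstract's aim.
- Keep the t-test or Mann–Whitney result as descriptive evidence of association.

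In section 3.1.2, rest the statement on TRIP's relevance on kappa and the AUC with their confidence intervals, not on the p-value. The AUC should stand beside kappa and not replace it, because it measures discrimination and not agreement.

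The cost is a few sentences and some added output: 16 scores × 3 opinions = 48 AUCs, all from data already collected. Some results may look less favorable than a p-value would suggest.

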### Expected results

2.4

As this is an exploratory study, no assumptions are made concerning concordances between the different professional opinions. However, in light of the literature concerning coping strategies used by people with npABI, we can expect some results:

In the event of an unfavorable opinion on the neuropsychological assessment and a favorable opinion on RDA, we should observe high compensation scores on the TRIP, as well as a low score on the BIDSAM, indicating good metacognition enabling the driver to adapt their driving to their difficulties.

In the event of an unfavorable opinion on both the neuropsychological assessment and RDA, we should observe low compensation scores on the TRIP and a high score on the BIDSAM, indicating a low awareness of difficulties that does not allow the use of compensatory strategies.

TRIP compensation scores and the BIDSAM score should be good predictors of road risk.

## Discussion

3

Driving activity is associated with greater community participation, better functional outcomes, fewer symptoms of depression, and greater life satisfaction (Novack et al., 2021). For these reasons, resuming driving represents a major challenge for people with npABI. However, in order to limit the increased road risk to which this population is exposed (Formisano et al., 2005; Bellagamba et al., 2020; Lundqvist et al., 2008), regulations require them to undergo a medical examination (Légifrance, 2022). Although the HAS recommendation (Haute Autorité de Santé, 2016) guidelines the multiprofessional evaluation, the decision-making process for maintaining the driving license of people with npABI has yet to be defined. This study will underpin good practice recommendations certified by the HAS, which are currently based on expert agreement. By gathering scientific evidence, this study aims to standardize the evaluation and support process for people with npABI who need to resume driving.

### Cross-sectional study

3.1

Thanks to the development of a multiprofessional evaluation protocol based on HAS recommendations, results will support the relevance of assessments recommended by the experts, and help refine their practical application (tools and methods). Concordance analysis will clarify the relevance of each assessment (neuropsychological, on-road and multiprofessional).

#### Relevance of the neuropsychological assessment

3.1.1

- In the event of concordance between the neuropsychologist’s opinion and other assessments (RDA, multiprofessional, approved doctor’s opinion), the neuropsychological assessment can then be considered to be a good predictor of driving ability, particularly by shedding light on the driving restrictions to be recommended.- In the event of a discrepancy between the neuropsychologist’s opinion and other assessments (RDA, multiprofessional, approved doctor’s opinion), the neuropsychological assessment cannot be considered a reliable predictor of driving ability, in line with the mixed findings reported in the literature (Wolfe and Lehockey, 2016; McKay et al., 2016; Ortoleva et al., 2012). However, this assessment will still be of obvious interest for detecting any reduction in useful field of view, raising awareness of certain deficits, or suggesting rehabilitation options adapted to the person’s cognitive profile. The neuropsychologist’s role is decisive in the project to resume driving (Perna et al., 2021).- Neuropsychological tests whose scores are significantly correlated with the TRIP score can be considered the most predictive of driving ability. These results will help guide the choice of neuropsychological tools.

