### The multiprofessional evaluation

1.3

An expert group issued good practice recommendations concerning the driving ability evaluation after npABI, which were certified in 2016 by the French National Authority for Health (Haute Autorité de Santé, HAS). These recommendations aim to standardize the decision-making process of the driving ability evaluation (Haute Autorité de Santé, 2016). This guide helps to identify, assess and support people with npABI who wish to resume driving. According to these recommendations, a multiprofessional evaluation should be carried out prior to any resumption (12th recommendation). Assessments are based on (a) visual functions, with ophthalmological evaluation recommended in the event of any doubt about an alteration of the visual pathway, (b) sensory-motor functions, with an on-Road Driving Assessment (RDA) recommended in the event of sensory-motor sequelae, and (c) cognitive functions, with the recommendation to carry out an RDA in cases of cognitive-behavioral sequelae. In practice, this multiprofessional evaluation takes place in a rehabilitation center, and should include an occupational therapy assessment, a neuropsychological assessment and an RDA with a driving instructor and a therapist. The PRM doctor integrates the medical component of this multiprofessional evaluation (requesting additional tests if necessary) and submits an advisory opinion to the approved doctor on the person’s ability to resume driving. The present field research focuses on studying the performance of the neuropsychological assessment and on-road assessment, integrated into the multiprofessional evaluation, with a view to harmonizing and improving practices.

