##### Neuropsychological assessment

2.2.1.2

This assessment is carried out by a psychologist specialized in neuropsychology. It includes a series of validated standardized tests investigating attentional, executive and psycho-behavioral functions. The list of tests was co-constructed according to different criteria:- psychometric qualities (sensitivity, validity, reliability)- relevance established in the literature in relation to driving ability evaluation- availability and frequency of use in current practice (assessed through a survey of rehabilitation centers)- administration conditions (essentially non-verbal tests for use with patients with expressive aphasia; non-bimanual tests allowing inclusion of patients with hemicorporeal deficits; duration deemed acceptable and equipment easy to obtain and use).

The neuropsychological assessment lasts around 3 h, divided into two one-and-a-half-hour sessions, each with a five- to ten-minute break. The order of administration of the tests was established so as to alternate tasks according to their format (computerized vs. paper-and-pencil), their mental load (higher or lower), their sensitivity to fatigue, and the cognitive functions called upon. The standardized neuropsychological assessment protocol is described in the case report form. It includes the following tests: Alertness (TAP 2.3.1), Divided attention (TAP 2.3.1), Epworth scale, Trail-Making-Test (TMT), Go/Nogo (TAP 2.3.1), Basic Empathy Scale in Adults (BES-A), Neglect with central task (TAP 2.3.1), Tour of London (TOLDX 2^nd^ edition), Working memory difficulty level 3 (TAP 2.3.1), Sustained attention color-or-form version (TAP 2.3.1) and UPPS Impulsive Behavior Scale. Lastly, the Brain Injury Driving Self-Awareness Measure—BIDSAM (Gooden et al., 2017) is part of the neuropsychological assessment, but will be completed following the RDA.

For each test, the examiner collects raw and standardized scores (each participant’s performance is compared to the standard group). Based on this assessment, the neuropsychologist then issues an opinion (favorable, unfavorable or reserved) on the estimated compatibility between the participant’s cognitive functions and the return to driving.

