##### Occupational therapy assessment

2.2.1.3

The occupational therapist carries out this assessment according to a non-standardized protocol, in order to investigate the participant’s sensory-motor functions, and to consider possible vehicle adaptations. His role is mainly to determine the necessary adaptation of the participant’s car and, thanks to the pluriprofessional advice given at the end of the process, to pass on his opinion to the approved doctor. The occupational therapist also administers questionnaires to obtain information on the participant’s driving before brain injury: Driving Habits Questionnaire (DHQ), Driving Behavior Questionnaire (DBQ) and perceived road risk.

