##### Multiprofessional synthesis

2.2.1.5

Professionals then work together to issue a joint opinion (favorable, unfavorable or reserved) on the participant’s driving ability, based on the assessments carried out.

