### Analysis

2.3

Participant characteristics and assets will be described and compared. Reasons for refusing to participate will be collected. Descriptive statistics on participant characteristics will be presented. The characteristics of participants included will be compared with those of non-included participants in the eligibility register to ensure their representativeness. Quantitative variables will be described in terms of mean, standard deviation, median, interquartile range and extreme values. Qualitative variables will be described in terms of absolute frequency and percentage per modality. The alpha threshold for statistical significance is set at 5%; 95% confidence intervals will be presented. All the variables collected for people included in the study will be described. Missing data will not be replaced in this study and some participants might be secondary excluded from certain analyses. Sub-group analyses may be carried out, if statistically robust, depending on the number of fitted cars required and the conclusion of the medical examination.

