##### Main criterion: concordance between professional assessments

2.3.1.1

To meet the main objective, the concordance of the results of the neuropsychological assessment, RDA and multiprofessional evaluation will be studied in pairs (agreement between professional assessments). Each professional involved in the study will give a “favorable,” “reserved” or “unfavorable” opinion based on their practice. Evaluation criteria will correspond to cross-tabulated numerical values of results from each assessment tool studied (neuropsychological assessment, RDA and multiprofessional evaluation). “Reserved” opinions indicating driving restrictions will initially be classified as “unfavorable,” so that the results can be expressed as a binary Favorable/Unfavorable variable for each assessment. The RDA results will also include the number of driving instructor interventions on pedals, steering wheel and other car controls, using categorical variables. The values *a*, *b*, *c* and *d* (Table 1) will be used to perform the concordance test detailed in the next section (“Statistical analysis”).

**Table 1 tab1:** Evaluation criterion of the main objective for contingency table.

		Assessment x_i_	
		Favorable	Unfavorable
Assessment x_ii_	Favorable	*a*	*b*
	Unfavorable	*c*	*d*

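### The neuropsychologist judges cognition only, but section 3.1.1 reads any disagreement with whole-driver opinions as unreliability, without separating sensory-motor or visual reasons

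*Protocol article*

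**What the plan says.** Section 2.2.1.2 restricts the neuropsychologist's opinion to one question. It is given "on the estimated compatibility between the participant’s cognitive functions and the return to driving". The same section explains how the tests were chosen, including "non-bimanual tests allowing inclusion of patients with hemicorporeal deficits", so patients with one-sided motor deficits are meant to be in the sample.

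The comparators are wider:
- **On-road assessment (RDA).** The opinion in section 2.2.1.4 concerns driving ability in general. Section 1.3 lists, among the parts of the evaluation, "sensory-motor functions, with an on-Road Driving Assessment (RDA) recommended in the event of sensory-motor sequelae".
- **Multiprofessional opinion.** Section 2.2.1.5 places it "on the participant’s driving ability, based on the assessments carried out". One of those assessments is the occupational therapist's, carried out "in order to investigate the participant’s sensory-motor functions, and to consider possible vehicle adaptations" (section 2.2.1.3). Section 1.3 adds visual functions and a medical component.
- **Approved doctor.** The participant takes the multiprofessional report to this visit (sections 2.2.1.6 and 2.2.1.7), and the outcome is fitness, limited fitness or unfitness.

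Under the main criterion (section 2.3.1.1), "the concordance of the results of the neuropsychological assessment, RDA and multiprofessional evaluation will be studied in pairs". Each opinion becomes binary, with reserved opinions at first grouped with unfavorable ones. Agreement is summarised by percentage and simple kappa (section 2.3.3). Section 3.1.1 states the reading in case of discrepancy with the other assessments: "the neuropsychological assessment cannot be considered a reliable predictor of driving ability".

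**The concern.** An opinion about one component of fitness is cross-tabulated with opinions about the whole. Take a patient whose cognition is rightly judged compatible with driving, and whose on-road or joint opinion is reserved because of a hemiparesis. That patient falls in a discordant cell although neither assessor is wrong. The table cannot tell this patient from one whose cognitive deficit the neuropsychologist missed, and section 3.1.1 reads both the same way.

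Two of the three primary pairs are affected (neuropsychology with RDA, and neuropsychology with the multiprofessional opinion), as is the neuropsychology part of secondary criterion A. The reading matters because section 3.4.2 notes that the decree omits neuropsychological assessment and hopes the study will give invisible disabilities more weight. A scope difference read as unreliability would bear on that question for a reason unrelated to how well cognition was assessed.

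**Working it through.** The plan gives no figure on this point, so there is none to reproduce. The first two steps compare the text; the third illustrates possible size.

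**1. Can non-cognitive reasons occur in this sample?** Yes. Section 2.1 removes contraindications other than the brain injury, so sensory-motor and visual sequelae of the injury itself remain. Section 2.2.1.2 accommodates motor deficits in the choice of tests, and section 2.3 anticipates fitted cars.

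**2. Does the plan separate them?** Section 2.3.1.1 records the verdict and not its ground. Section 3.1.2 treats RDA discrepancies differently: they may be examined by comparator and by direction, and the value of the RDA is held to stand. Its only account of a neuropsychology-RDA discrepancy is coping linked to awareness. Section 2.4 shows that this account fits the cell with neuropsychology unfavorable and RDA favorable. A purely motor reason falls in the opposite cell, for which no explanation is offered.

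**3. How large could the effect be?** All inputs here are assumptions:
- p = share non-favorable on cognitive grounds
- g = probability that neuropsychology matches the cognitive status
- f = further share non-favorable only on non-cognitive grounds

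Cells (neuropsychology / comparator):
- favorable / favorable = (1 − p − f)g
- favorable / non-favorable = p(1 − g) + fg
- unfavorable / favorable = (1 − p − f)(1 − g)
- unfavorable / non-favorable = pg + f(1 − g)

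Observed agreement Po is the sum of the first and last cells. Pe is the chance agreement from the margins. Kappa = (Po − Pe)/(1 − Pe).

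Worked case, p = 0.40, g = 0.90, f = 0.10: the cells are 0.45, 0.13, 0.05 and 0.37. Po = 0.82. Pe = 0.58 × 0.50 + 0.42 × 0.50 = 0.50. Kappa = 0.32/0.50 = 0.64.

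| f | Agreement, g = 0.90 | Kappa, g = 0.90 | Kappa, g = 0.80 |
|---|---|---|---|
| 0 | 90% | 0.79 | 0.59 |
| 5% | 86% | 0.72 | 0.53 |
| 10% | 82% | 0.64 | 0.48 |
| 15% | 78% | 0.57 | 0.43 |
| 20% | 74% | 0.50 | 0.38 |

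Setting p to 0.30 or 0.50 moves each kappa by about 0.03 at most.

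A second illustration makes neuropsychology always right on cognition, with 30% cognitively unfit and 20% of the remaining 70% non-favorable for another reason. The discordant share is 0.70 × 0.20 = 14%, or 14 of 100 participants. Po = 0.86, Pe = 0.70 × 0.56 + 0.30 × 0.44 = 0.524, and kappa = 0.336/0.476 = 0.71.

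Neither model lets the comparator use the neuropsychological result. They are closest to the RDA pair and do not give a net effect for the other two.

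**The case against.** Several counter-arguments have force.

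- **The plan has partial safeguards.** Section 2.3 says "Sub-group analyses may be carried out, if statistically robust, depending on the number of fitted cars required" and goes on to name the conclusion of the medical examination as a second subgroup variable. Reserved opinions are merged only initially. Test scores are also correlated with the TRIP on-road grid (section 2.3.1.2.2), and section 3.1.2 allows exploration by direction. These stand as mitigation. But the subgroups are optional, none of these steps uses the reason for the opinion, and none alters section 3.1.1.
- **The scope gap is narrower than it first looks.** Other incompatible conditions are excluded. The battery includes a neglect test, and section 3.1.1 credits the assessment with detecting a reduced useful field of view. This stands: the main route is sensory-motor, with visual reasons only in part.
- **The reading may be literally true.** An opinion that ignores motor limits does predict overall driving ability less well. The passage is discussion text in an exploratory study, sets no kappa threshold, and goes on to affirm other uses of the assessment. This stands as far as it goes, but low agreement from scope does not show unreliability in what was assessed.
- **Agreement may be pushed up.** The joint opinion uses the neuropsychological assessment, and the doctor receives the resulting report. A reader might infer that all neuropsychology comparisons are biased towards discordance. The documents do not support that: for these two comparators the forces oppose each other and neither is quantified.
- **Small shifts may not be visible.** At f = 5%, kappa drops by about 0.08, less than the approximate 95% half-width of 0.12 with 100 participants. That is fair, but a scope difference is systematic and does not average out.

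**Conclusion.** The point holds as one of interpretation. A cognition-only opinion is compared with whole-driver opinions, the reason for a non-favorable opinion is not carried into the table, and section 3.1.1 draws a conclusion about reliability from any discrepancy. This follows from the text and needs no assumed figure.

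The size is unknown. The kappa values above rest wholly on assumed shares, and nothing in the article shows how often a non-favorable opinion is purely sensory-motor or visual. A reader might also infer that the study is set to conclude against neuropsychological assessment. The text does not go that far: no cut-off is fixed, other uses are affirmed, and the net direction is open for the multiprofessional and doctor pairs. What can be said is that the planned tables cannot separate a scope difference from a missed cognitive problem, and the stated reading assumes the latter.

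**What to change.** 1. Keep the all-reasons concordance table in section 2.3.1.1 and criterion A as the main result.
2. For each neuropsychology pair, report the two discordant cells separately by direction.
3. Split the cell with neuropsychology favorable and comparator non-favorable by reason, taken from the multiprofessional report and the RDA record: cognitive-behavioral or both; sensory-motor or visual only; not stated. Present this as a supplementary row or sensitivity analysis, not as a replacement. Dropping participants according to the comparator's verdict and reason would raise kappa by construction.
4. Reword section 3.1.1 so that discordance documented as purely sensory-motor or visual is read as a difference in scope, and only the remaining discordance counts against neuropsychology as a predictor.

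The RDA-multiprofessional comparison is unchanged and no new patient procedure is needed. The cost is one coded reason per participant in that cell and a supplementary row per pair. Coding takes some judgment and is best done without sight of the neuropsychological opinion where possible, since a favorable opinion could steer the coder towards a non-cognitive label. The reports may not always state a reason. The approved doctor's reason may be unavailable, because the participant relays that opinion, so the category for reasons not stated should be reported openly. If the full case report form, which is not shown, already records reasons, only the tabulation and the wording need to change.
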